**2. Providing auditory spatial training (intervention group only)**

Auditory spatial training is designed based on five signs that are important in informational masking release: angular differentiation between target and competing signals
^16,
34–
36^; signal to noise ratio
^34^; similarity and difference between the target and competing signals
^12^; similar or different gender for target and competing signals
^12,
37^; and meaningfulness of the competing signal
^12^. As one of the main principles of any auditory training program is progression in difficulty so the training sessions will be divided into three general steps by considering the competing signals. In the first step, meaningless competing signals will be used like white noise. In the second step, in order to make the training process somewhat difficult, meaning-carrying signals like speech babble consisting of four speakers will be used. Finally, for making more difficulty, sentence materials with male and female genders will be used. The reason for using the gender factor is that consideration of gender similarity or difference between target and competing signals is one of the signs that adults use for informational masking release
^12,
37^.

In all steps, the target signal will be presented from the loudspeaker at 0-azimuth degree and competing signals from different azimuth angles such as ±45, ±90 and 0
^38,
39^. Therefore, the difficulty of training will grow in each step by reducing the azimuth angle of the competing signal
^40^.

Sentence signals are selected from Persian version of QuickSIN
^41^. Every step of training is implemented as follows:

The intensity of the competing signal is fixed at 60 dBSPL, and at the beginning the intensity of target signals is 70 dBSPL. Three first sentences will be used for familiarization. If an individual needs more practice, more familiarization sentences will be provided.

An individual will be requested to identify the keywords heard in the target sentences. In the case of true and false identification, required feedback will be provided. If the individual identifies more than 50% of the keywords, the sentence will be considered true. In this signal to noise ratio, 5 sentences will be provided where if the individual identifies more than 50% of the presented sentences, the signal to noise ratio decreases in 5dB steps, after which 5 sentences will be provided again for the individual. If the individual does not have the capability to correctly identify more than 50% of the presented sentences in each signal to noise ratio, the training begins where this signal to noise ratio will be considered as the initial level. The training will continue for 20 minutes and the intensity will change in an adaptive procedure, such that in the case of correct identification of a sentence, the intensity will be decreased by 1.5dB while it will be increased by 2.5 dB if the individual scored less than 50% of words correctly. At each intensity where an individual can correctly identify the sentences, the next sentence will be presented and the above process will repeat.

The optimal condition for perceptual auditory learning includes active listening to high repetition of signals during the consecutive educational sessions, which is conducted within a short time interval. Since long-term training is not a very suitable option in the clinic
^2^, trainings will be repeated three times a week completed in 5-week cycles
^42^.

**3. Assessments after auditory spatial training (interview immediately after and five weeks after training)**

The informational masking test (as per Part 1) will be done immediately after training and five weeks after that using the Persian list of the coordinate response measure (CRM) corpus, which will be compared with the pre-training results (preliminary interview). This score will be the primary outcome. The reason for repeating experiments five weeks after the intervention is determining the reliability of the results obtained by intervention for informational masking release.

The informational masking release value will be calculated based on the difference between sentence recognition score (in all 30 conditions of signal to noise, different spatial angles, and two genders) in both noise situations (meaningful and non-understandable). The changes in informational masking in the assessments will be calculated before and after the intervention across all 30 conditions (see
Table S2, Extended data).

The ‘synthetic sentence identification test’
^32^ and the ‘Persian Reading Span test’ score
^33^.also will be evaluated immediately after training and 5 weeks after that.

As the ultimate purpose of this research is improving the quality of speech perception of elderly people, the score of SSQ immediately and 5 weeks after intervention will be obtained and the results of both intervention and control groups will be compared separately. This score and the scores of ‘synthetic sentence identification test’ and ‘Persian reading span test’ will be the secondary outcomes of the interventions.
Figure S2 (Extended data) represents participant’s timeline of the second part of the study.

### Sample size

***Part 1.*** The study of Terwee
*et al.* was considered as the basic study to determine the sample size of the first part of our study. They suggested that at least 50 patients in each group must be included to evaluate the construct validity
^43^. In total, 50 young people aged between 20 and 40 years and 50 elderly people aged between 60 and 75 years, with normal peripheral hearing who do not suffer from speech understanding in noisy environments, will be recruited.

***Part 2.*** The following formula is used to determine the sample size:

$$\text{n}=\frac{{\left(Z_{1-\alpha /2}+Z_{1-\beta }\right)}^{2}\left({S_{1}}^{2}+{S_{2}}^{2}\right)}{\left(\mu_{1}-\mu_{2}\right)}$$

n= (Z1−α/2+Z1−β)2(S12+S22)(μ1−μ2)

S
_1_: standard deviation of the studied variable in the first group (case, exposed, or intervened)

S
_2_: standard deviation of the studied variable in the second group (control, unexposed, or compared)

µ
_1_: mean of the studied variable in the first group

µ
_2_: mean of the studied variable in the second group

α=0.05

β=80%

Z= 1.96

In this formula, the studied variable is the extent of informational masking changes before and after the intervention. There is no previous study, which was used the same training as this study proposes; therefore, we considered the study of Delphi
*et al.* which was on a group of elderly individuals
^44^. In her study the mean and standard deviation of the improvement in the main variable were 37.5 and 25.17 in the experimental group and 25.17 and 18.15 in the control group, respectively. According to this, the sample size calculated 14 in each group. By assuming 20% drop out, so we will use 18 people in each group.

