### Study design, setting and participants

This research will be conducted in the Audiology Clinic of Rehabilitation School of Iran University of Medical Sciences.

This study consists of two main parts. Part 1: develop and determine an informational masking measurement test and explain its validity characteristics in a test development study, conducted cross-sectionally. The study population will be a group of elderly (60 to 75 years old) and a group of young (20 to 40 years old) people. The young people will be recruited from rehabilitation students of Iran University of Medical Sciences, while elderly people are those referred to the audiology clinics of Iran University of Medical Sciences.

Part 2 (simple randomized clinical trial): the effect of training on informational masking release. This part of study is a simple randomized clinical trial design and patients will be randomly assigned into two groups of control (not receiving auditory spatial training) and intervention (receiving auditory spatial training). The random allocation will be performed based on balanced randomization [1:1] where the allocation will be applied by random number table (those assigned an odd number, control group; those assigned an even number, intervention group). This allocation sequence will be generated by one of the audiology clinic staff of the IUMS who will not have any role in the study. An elderly population, 60–75-years-old, who are referred to the audiology clinics of Iran University of Medical Sciences will be selected. The two groups will be matched for age and gender. Those in the control group will not receive any rehabilitation programs during the study.

*Inclusion criteria (for all participants in the study):* auditory thresholds ≤25dB within the 250–8000Hz frequency range for ensuring the normal pure tone audiogram or normal peripheral hearing, ensuring lack of salient cognitive problems using Mini Mental State Examination (MMSE)
^26^; having diploma or higher degree; right-handedness (using Edinburgh handedness inventory); speaking Farsi and being monolingual; complaint about speech in noise perception difficulties (just for those in part 2 of the study); and normal condition of middle ear function.

*Exclusion criteria (for all participants in the study):* unwillingness for participation in each step of research and not meeting inclusion criteria.

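### The Part 2 sample size of 14 per group cannot be reproduced: the formula as printed gives 613, the standard formula gives 50, and the repeated 25.17 leaves the inputs themselves in doubt

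*Protocol article*

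**What the plan says.** The Part 2 paragraph of the protocol article's Sample size section gives a formula for comparing two means. The numerator is the squared sum of two normal quantiles times the sum of the two variances. The denominator is the difference in means, with no square. The listed settings are α = 0.05, β = 80% and Z = 1.96.

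The variable used for sizing is a change score: "the studied variable is the extent of informational masking changes before and after the intervention". The planning values are borrowed from an earlier training study in elderly people, in which "the mean and standard deviation of the improvement in the main variable were 37.5 and 25.17 in the experimental group". For controls, the same sentence gives a mean of 25.17 with an SD of 18.15.

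The section then states: "According to this, the sample size calculated 14 in each group". Allowance for attrition follows: "By assuming 20% drop out, so we will use 18 people in each group". Allocation is "balanced randomization [1:1]" under Study design, setting and participants.

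**The concern.** Formula, inputs and result stand together in one paragraph, so the calculation can be checked directly, and it does not close. Three features point to a fault:

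- The denominator lacks its square, both in the displayed equation and in the plain-text line below it. The plain-text line keeps the other exponents, so loss in text extraction is an unlikely explanation.
- β is given as 80%, which is the usual value for power, not for the type II error rate.
- The figure 25.17 appears twice in different roles, as the experimental SD and as the control mean.

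The sample size is the protocol's only statement of what the trial can detect. If the printed inputs are right, the trial is far smaller than its own planning effect requires. If an input is wrong, the printed justification describes a different effect from the one actually planned on. A reader cannot tell which.

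**Working it through.** **Inputs** (Sample size, Part 2, unless noted)

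- Improvement, experimental group: mean 37.5, SD 25.17
- Improvement, control group: mean 25.17, SD 18.15
- α = 0.05, two-sided, Z = 1.960
- Power 80%, Z = 0.8416 (an interpretation; the text prints β = 80%)
- Allocation 1:1 (Study design, setting and participants)
- Dropout 20%

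**Derived quantities**

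- Difference: 37.5 − 25.17 = 12.33; squared, 152.03
- Sum of variances: 25.17² + 18.15² = 633.53 + 329.42 = 962.95
- Root-mean-square SD: √(962.95/2) = 21.94; standardised effect 12.33/21.94 = 0.562
- (1.960 + 0.8416)² = 7.849; numerator 7.849 × 962.95 ≈ 7558

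**Attempt to reproduce 14**

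| Reading | Calculation | n per group |
|---|---|---|
| Formula as printed, power 80% | 7558 / 12.33 | 613 |
| Standard formula, difference squared, power 80% | 7558 / 152.03 = 49.7 | 50 |
| Squared, β literally 0.80 | (1.960 − 0.8416)² × 962.95 / 152.03 = 7.9 | 8 |
| Unsquared, β literally 0.80 | (1.960 − 0.8416)² × 962.95 / 12.33 = 97.7 | 98 |
| Squared, one-sided 5%, power 80% | 39.2 | 40 |
| Squared, only Z = 1.96 used | 1.96² × 962.95 / 152.03 = 24.3 | 25 |

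With the noncentral t distribution in place of the normal approximation, 50 becomes 51. None of these readings gives 14. Some invalid shortcuts do land there. For example, 1.96² × (25.17 + 18.15) / 12.33 = 13.5, which uses unsquared SDs and drops the power term. That is a coincidence of arithmetic and does not show how the figure was obtained.

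**Dropout step.** 14 / 0.8 = 17.5, rounded up to 18. This step is correct. Applied to 50, it would give 50 / 0.8 = 62.5, so 63.

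**What input would give 14?** With the printed SDs, the difference needed is √(7558 / 14) = 23.2. The control mean would then be 37.5 − 23.2 = 14.3 in place of 25.17.

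**Power if the printed inputs are right** (two-sided 5% t-test on change scores, noncentral t)

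| Completers per group | Power for 12.33 points | Difference detectable with 80% power |
|---|---|---|
| 14 | 29.9% | 24.1 points |
| 18 | 37.4% | 21.1 points |

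The detectable differences are 24.1/12.33 = 1.95 and 21.1/12.33 = 1.71 times the planning difference.

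**The case against.** The strongest reply is that the result may be right and an input wrong. If only the control mean was miscopied and its true value is near 14.3, 14 per group is about what the standard formula gives. Power is then about 77% with 14 completers and 87% with 18, by the noncentral t. The repeated 25.17 makes this plausible. This stands, and it limits the conclusion: a reader might infer that the trial simply has 30% power, but the document does not establish that. It establishes that the printed calculation is not reproducible. Low power follows only if the printed inputs are confirmed, and even then 30% applies to 14 completers, while 18 per group are planned.

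A reader might also say that the stated formula gives 50. It does not. Fifty comes from the standard formula, and the one printed gives 613.

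The intended 80% power is itself an inference. The text never states a power, only β = 80%. Reading this as a labelling slip is reasonable, because a literal β of 0.80 would mean planning for 20% power, and it does not yield 14 either.

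Finally, the Data analysis section plans repeated measures ANOVA over three assessments, whose exact power cannot be derived from the document. The figures above are therefore approximate. But the sizing variable is already a before–after change, so the within-person gain is in the inputs. Reducing 49.7 to 14 by covariate adjustment alone would need a correlation with the change score of √(1 − 14/49.7) ≈ 0.85, and no such adjustment is claimed.

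**Conclusion.** The point holds as a failure of reproducibility. On the inputs given, 14 per group follows neither from the formula as printed (613) nor from its standard form (50, or 51 by t-test), and no other section repairs it. The missing square and the mislabelled β are errors in their own right, and correcting both leads to 50, not 14.

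How much this matters for the trial depends on the inputs. If they are right, power for the planning difference is about 30% to 37%, under half of the intended 80%. If the control mean was miscopied and is near 14.3, the sample size is roughly adequate and only the text needs correcting. The document cannot decide between the two. The power figures assume a two-sided 5% comparison of change scores with the printed SDs and equal groups.

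**What to change.** 1. Square the difference in means in the denominator.
2. Replace β = 80% with power 80% (β = 0.20).
3. Check all four planning values against the source study, the repeated 25.17 first.
4. If a value was miscopied, correct it and show the calculation that leads to 14.
5. If the values are confirmed, replace the implied 80% power with what the design delivers: about 30% (14 completers per group) to 37% (18 per group) for 12.33 points. Alternatively, state that 80% power is reached only for true differences of about 24 or 21 points respectively.

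The cost is a wording change to one paragraph and a check of the source, with the amendment sent to the ethics committee as the protocol already provides. No extra participants are needed for this correction. If the inputs are confirmed, however, the stated power becomes less favourable and the trial remains small for its planning effect. The Study status section says that enrolment has been performed and allocation is still to come, so the correction can be made before groups are assigned.

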### Data analysis

Central tendency and dispersion indices (mean and standard deviation) will be used in descriptive analysis of data. In data analysis and for determining the reliability of the Persian version of the coordinate response measure (CRM) corpus, paired t-test and Pearson correlation will be used in the case of normality of data; otherwise, Spearman test will be employed, and one-way ANOVA will be utilized for determining intra-class correlation coefficient.

In part 2 of the research, repeated measures ANOVA values will be used for inter-group comparisons and two-way ANOVA will be employed for comparison among groups. SPSS software (V20.0, IBM Corporation, New York, USA) will be used for statistical data analysis and the significance level for all tests will be 0.05.

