^25^ where each of the sentences will be filtered using a band pass filter of 80 to 8000 Hz filter. Again, in order to determine the face validity, the recorded sentences will be given to the experts mentioned above to determine their suitability. They must fill the questionnaire, which will be emailed to them.

To determine the reliability of CRM speech materials, the mean scores of CRM recognition in the silent will be evaluated in a group of young and old people with normal peripheral hearing who do not have speech perception difficulties in noisy environments. There will be one preliminary test and then a re-test. This evaluation will be implemented at the comfort hearing level of the participants. The score will be calculated based on the correct recognition percentage of the sentences. A sentence will receive a correct score when the color-number combination recognition is recognized correctly
^25,
27^. In this study, the mean correct score for color, number, and noun will be studied separately in order to calculate the error percentage for each of them
^24^. By preparing these sentences, they can be used in the part 2 of the study.

The best way to measure informational masking score is determining the score for speech recognition in the presence of meaningful and meaningless competing noise. To this end, the recognition score for Persian version of CRM speech corpus will be measured under two conditions:

**A.**
*In the presence of meaningful competing noise:* The competing signal will be selected from the Persian version of CRM corpus, where the call sign, color and number used in the competing sentence will be different from those of the target sentence and it will be expressed by a different speaker. The individual will be trained to pay attention to certain target call signs and ignore other signals
^24,
25,
27^. As one of the important effective factors for informational masking is the great similarity between target and competing signals (like when both of them are speech)
^7,
8^, using CRM sentences as both the target signal and competing signal, the high semantic and syntactic similarity would develop between target and competing signals
^24,
25^.
**B.**

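### In the Part 1 reliability analysis, non-normal data remove the only test of a shift between test and re-test, because Spearman alone replaces both the paired t-test and Pearson

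*Protocol article*

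**What the plan says.** Under Study procedures, Part 1, CRM recognition is scored as percent correct in quiet, at each listener's comfort level, in young and older people with normal peripheral hearing and no difficulty with speech in noise. The design is one repeat: "There will be one preliminary test and then a re-test".

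Under Data analysis, the methods for this comparison are: "paired t-test and Pearson correlation will be used in the case of normality of data; otherwise, Spearman test will be employed". The same sentence then adds that "one-way ANOVA will be utilized for determining intra-class correlation coefficient", with no normality condition, so the ICC belongs to both branches. The section ends by stating that "the significance level for all tests will be 0.05".

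Under Sample size, Part 1 has 50 young and 50 older participants. The basis is a published rule that "at least 50 patients in each group must be included to evaluate the construct validity". It is not a calculation for the reliability analysis. The article gives no expected correlation, no expected test/re-test change and no acceptance value for reliability.

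**The concern.** A test/re-test study asks two things: whether listeners keep their relative positions, and whether scores drift as a whole. The normal branch has one procedure for each. When normality fails, one procedure replaces both, and it is the rank counterpart of Pearson only. The rank counterpart of the paired t-test is missing. The plan thus treats a shift test as part of reliability and then drops it on the outcome of a normality check.

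That check may well fail. Percent-correct scores in quiet, in listeners with normal hearing, are bounded at 100 and plausibly close to it.

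What is at stake is what Part 1 can say about practice effects. The test built on this corpus is given at three assessments in Part 2, and the Discussion offers the corpus and its reliability for wider research use, where there may be no control group to absorb drift.

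**Working it through.** The plan gives no computed figure for reliability, so there is nothing to reproduce. The checks below take n = 50 per age group (or 100 pooled) and the 0.05 level from the article. Assumed: two-sided tests, all Part 1 participants contributing to reliability, and the correlations, shifts and score distributions stated in each step.

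**1. Spearman and a constant shift.** Spearman's rho is the correlation of the ranks of x (test) with the ranks of y (re-test). Replacing y by y + c leaves every rank of y unchanged, so rho and its p-value are unchanged for any c. Its rejection rate carries no information about c.

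**2. What the normal branch would detect.** For a shift of 0.5 SD of the paired differences, the noncentrality is 0.5 × √50 = 3.54 on 49 degrees of freedom, which gives power 0.934. At n = 100 it is 0.5 × √100 = 5, with power 0.999. This is the capability lost on switching branch.

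**3. Skewed scores, n = 50, 1,500 runs per cell, shift in SD of the scores.**

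| Underlying correlation | Shift | Mean Spearman rho | Mean one-way ICC | Wilcoxon signed-rank rejects |
|---|---|---|---|---|
| 0.9 | 0 | 0.88 | 0.87 | 4.5% |
| 0.9 | 0.5 | 0.88 | 0.75 | 100% |
| 0.9 | 1 | 0.88 | 0.47 | 100% |
| 0.4 | 0 | 0.37 | 0.34 | 5.1% |
| 0.4 | 0.5 | 0.38 | 0.26 | 94.5% |
| 0.3 | 0 | 0.28 | 0.26 | 4.8% |
| 0.3 | 0.5 | 0.28 | 0.18 | 92.1% |

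**4. Why the one-way ICC does not replace the shift test.** With two sessions, score variance 1, correlation ρ and shift δ, the expected between-person mean square is 1 + ρ and the expected within-person mean square is (1 − ρ) + δ²/2. Then

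ICC ≈ (2ρ − δ²/2) / (2 + δ²/2).

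- ρ = 0.9, δ = 0: 1.8/2 = 0.90.
- ρ = 0.9, δ = 0.5: (1.8 − 0.125)/2.125 = 0.79.
- ρ = 0.9, δ = 1: (1.8 − 0.5)/2.5 = 0.52.

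An ICC of 0.52 therefore fits a corpus with correlation 0.9 and a 1 SD practice gain, and equally a corpus with correlation 0.52 and no gain. The one-way model has no session term with which to tell them apart.

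**5. A near-ceiling illustration.** Assumed: 50 listeners, 50 sentences, ability on the logit scale with mean 3 (about 95% correct) and SD 0.8, gain 0.6 logit (about 2.6 points); 3,000 runs.

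- Shapiro-Wilk rejects normality of the raw scores in about 100% of runs. It rejects normality of the differences in 52% without the shift and 79% with it.
- Spearman is significant in 99% without the shift and 97% with it.
- Wilcoxon signed-rank rejects in 5% without the shift and about 98% with it.
- The one-way ICC falls from 0.66 to about 0.46.

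**6. What a significant correlation shows.** The smallest significant r is t/√(n − 2 + t²). At n = 50, t = 2.011, giving 2.011/√(48 + 4.04) = 0.279. At n = 100, t = 1.984, giving 1.984/√(98 + 3.94) = 0.197. A true rank correlation of 0.4 is significant in about 81% of studies at n = 50 and 98% at n = 100 (Fisher z, variance factor 1.06). Pearson has the same null, so this applies to both branches.

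**The case against.** The strongest reply is the ICC in the same sentence. It carries no normality condition, and both drift and noise lower it. A reader might infer from step 6 that a poorly reliable corpus would be passed as reliable. The document does not support that. It nowhere says that a significant correlation establishes reliability, and with underlying correlations of 0.3 to 0.4 and no shift the mean ICC is only 0.26 to 0.34, so poor reliability would be visible. This part of the reply stands. What it leaves open is whether a low ICC reflects practice or noise.

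A reader might also infer that undetected drift biases the trial. It does not follow. In Part 2 a control group is assessed at the same three times, so drift common to both arms drops out of the comparison. The re-test is also done in quiet, whereas the primary outcome is a difference between two masked conditions.

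Third, the non-normal branch is not certain. The article does not say whether normality is checked on scores or on differences, and a paired t-test depends on the differences. In the illustration these fail the check in 52% to 79% of runs, not in nearly all. This stands too, so the branch is plausible rather than assured.

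Fourth, planned means and SDs would let a change be seen by eye, and a condensed article may leave companion tests to a fuller plan. The first half is fair, but a descriptive pair of means is no substitute for an estimated difference with its uncertainty. The second half is weaker: the article does not stay silent, it names the test to be used when normality fails.

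**Conclusion.** The concern holds in a limited form. When data are judged non-normal, the stated rule leaves Part 1 with no paired location test, and the test named in its place cannot respond to a systematic test/re-test shift. Against a shift of 0.5 SD of the differences, the lost capability is about 93% power at n = 50. A Wilcoxon signed-rank test would keep it (92% to 100% for a shift of 0.5 SD of the scores in the skewed simulations). The one-way ICC responds to a shift but mixes it with random error.

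The invariance of Spearman is exact and needs no assumption. The percentages rest on two-sided tests, full use of the Part 1 sample, and the assumed correlations, shifts and score distributions. The consequence is confined to validation of the corpus and does not touch the randomised comparison.

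**What to change.** In Data analysis, for the non-normal branch, state that a Wilcoxon signed-rank test on re-test minus test will be used alongside Spearman. Report the mean re-test minus test difference with a 95% CI, for example by bootstrap. State that reliability will be judged on the size of the ICC with its confidence interval, not on the p-value of a correlation.

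An acceptance value for the ICC, limits of agreement, a two-way ICC model, or dropping correlation p-values altogether would be reasonable additions, but they are largely a matter of preference and do not follow from this defect.

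The cost is a few lines of text and slightly more analysis, with no new data or participants. The downside is that the reliability result may look less favourable, since a visible drift or a wide interval around the ICC would have to be reported.

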## Abstract

**Background:** Regarding the strong auditory spatial plasticity capability of the central auditory system and the effect of short-term and long-term rehabilitation programs in elderly people, it seems that an auditory spatial training can help this population in informational masking release and better track speech in noisy environments. The main purposes of this study are developing an informational masking measurement test and an auditory spatial training program.

**Protocol:** This study will be conducted in two parts. Part 1: develop and determine the validity of an informational masking measurement test by recruiting two groups of young (n=50) and old (n=50) participants with normal hearing who have no difficulty in understanding speech in noisy environments. Part 2 (clinical trial): two groups of 60-75-year-olds with normal hearing, who complain about difficulty in speech perception in noisy environments, will participate as control and intervention groups to examine the effect of auditory spatial training. Intervention: 15 sessions of auditory spatial training. The informational masking measurement test and Speech, Spatial and Qualities of Hearing Scale will be compared before intervention, immediately after intervention, and five weeks after intervention between the two groups.

**Discussion:** Since auditory training programs do not deal with informational masking release, an auditory spatial training will be designed, aiming to improve hearing in noisy environments for elderly populations.

**Trial registration:** Iranian Registry of Clinical Trials (
IRCT20190118042404N1) on 25
^th^ February 2019.

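### The Part 2 analysis names two ANOVAs for one between-group question, does not say which term tests the training effect, and adjusts for baseline in neither

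*Protocol article*

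**What the plan says.** The Data analysis section gives Part 2 one sentence on method: "repeated measures ANOVA values will be used for inter-group comparisons and two-way ANOVA will be employed for comparison among groups". It adds that "the significance level for all tests will be 0.05".

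Other sections bear on what is to be tested:

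- The Abstract says the informational masking test and the SSQ "will be compared before intervention, immediately after intervention, and five weeks after intervention between the two groups".
- The Sample size section says "the studied variable is the extent of informational masking changes before and after the intervention", so the trial is sized on a between-group difference in change. It ends: "By assuming 20% drop out, so we will use 18 people in each group".
- The section on assessments after training says of the primary outcome: "The changes in informational masking in the assessments will be calculated before and after the intervention across all 30 conditions". For the SSQ, a secondary outcome, it says "the results of both intervention and control groups will be compared separately".

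The primary outcome is measured before training, immediately after it and five weeks later, so every participant is due to have a baseline score.

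**The concern.** Inter-group and among-groups are the same question. The plan therefore attaches two differently named methods to the decisive comparison, each at 0.05, with no rule for which one counts. A three-visit repeated measures ANOVA also offers two candidate terms, the group main effect and the group-by-time interaction. They test different things and can disagree.

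The group main effect is the term that the word inter-group most readily suggests. It averages in the pre-training visit, where randomisation makes the true difference zero, so an effect present at both later visits is shrunk to two thirds. The group-by-time term is a valid test of differential change, but it spends two degrees of freedom and leaves information unused. In a trial of 36 people, the baseline score is the cheapest precision available. An undetermined primary test also leaves the analyst to choose a term after seeing the data.

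**Working it through.** **Inputs from the protocol article.** 18 per group (14 after the planned dropout), three visits, 5% two-sided tests.

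**Assumptions, not in the documents.** Equal variances and one common within-person correlation r of 0.3, 0.5 or 0.7; a training effect d = 0.8 SD at both post visits. The plan states no power for any named test, so it has no figure to reproduce on this point.

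**Step 1: dilution.** The true group differences at the three visits are 0, d, d. Their average, which the group main effect tests, is 2d/3 = 0.53 SD when d = 0.8.

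**Step 2: signal in each test.** With n per group, the non-centrality (squared effect over its variance) is:

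- Group main effect: (n/2) × (4/3)d² / (1 + 2r)
- Group-by-time, 2 df: (n/2) × (2/3)d² / (1 − r)
- Baseline-adjusted (ANCOVA), first post visit: (n/2) × d² / (1 − r²)
- Baseline-adjusted, mean of both post visits: (n/2) × 2d² / [(1 − r)(1 + 2r)]

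For n = 18, d = 0.8, r = 0.5: 3.84, 7.68, 7.68 and 11.52. For r = 0.7: 3.2, 12.8, 11.29 and 16.0. The last quantity is the sum of the first two (3.84 + 7.68 = 11.52; 3.2 + 12.8 = 16.0). The adjusted contrast over both visits thus combines the information that the repeated measures ANOVA splits between two terms, whatever r or d is.

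**Step 3: power.** Simulation, 20,000 trials per setting, d = 0.8:

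| Test | 18 per group, r = 0.3 / 0.5 / 0.7 | 14 per group, r = 0.3 / 0.5 / 0.7 |
|---|---|---|
| Repeated measures, group term | 57% / 48% / 42% | 46% / 38% / 32% |
| Repeated measures, group-by-time | 53% / 68% / 89% | 42% / 56% / 79% |
| ANCOVA, first post visit | 67% / 76% / 89% | 55% / 64% / 80% |
| ANCOVA, mean of both post visits | 87% / 90% / 97% | 76% / 81% / 91% |

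Power computed from the Step 2 formulas agrees within about 2 points. Repeat simulations differ by about 1 point, for example 41% for the group term and 90% for first-visit ANCOVA at r = 0.7.

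**Step 4: error rates with no training effect.** The repeated measures group term, group-by-time term and ANCOVA all reject in about 5%. If a two-way ANOVA were run with the three visits as independent rows, the variance of the group difference would be understated by a factor 1 + 2r. The error rate of the group term would then be about 2[1 − Φ(1.96/√(1 + 2r))], which is 12%, 17% and 21% for r = 0.3, 0.5 and 0.7. Simulation gives 12%, 16% and 21%. On that same reading the group-by-time term rejects in 1.4% or less, so it is far too conservative.

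**The case against.** The strongest reply is that nothing in the text is invalid as written. A two-way ANOVA with group and time as factors can be a mixed design, which is the same valid model as the repeated measures ANOVA. The sample size is defined on change, which points to group-by-time, and that term nearly matches a single-visit ANCOVA when the correlation is 0.7. Covariates and missing-data handling are often left to an analysis plan that is not shown. Most of this stands. It does not settle which of two named methods, or which term, decides the trial, and at a correlation of 0.5 group-by-time still trails the two-visit adjusted contrast by 22 points (68% against 90%).

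Three stronger readings are tempting, and the documents do not support them:

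- **That the two-way ANOVA has an inflated error rate.** This needs repeated visits to be entered as independent rows. The protocol does not say so. Naming the method apart from repeated measures ANOVA only leaves that open, and only the group term would be inflated.
- **That benefit will be claimed from tests within each arm.** The phrase "the results of both intervention and control groups will be compared separately" belongs to the SSQ, and it could mean separately at each visit. The Abstract says the comparison is between groups. With no practice gain, a significant change in the trained arm alone occurs in about 5% of null trials. It takes an assumed gain of 0.5 SD in both arms, and a decision rule the protocol does not contain, to reach 19% to 25%.
- **That the plan loses about half its power.** This holds only if the group main effect is the test, and the text does not select it.

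On dropout, the move from 14 to 18 per group already budgets for the loss of numbers from complete-case analysis.

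**Conclusion.** The point holds as a badly fixed primary test and a free gain in precision. It is not a demonstrated error-rate failure. One between-group question has two methods, no designated term and no baseline adjustment.

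At 18 per group and 0.8 SD, the contrast over both post visits has more power than group-by-time by 22 points at a correlation of 0.5 and by 8 points at 0.7. Against the group main effect the gain is 42 points (90% against 48%) and about 55 points (97% against 42%).

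The sizes depend on an effect and a correlation that the documents do not give. The plan's own planning figures imply a smaller standardised effect on the change scale: (37.5 − 25.17) / √[(25.17² + 18.15²)/2] = 12.33/21.94 = 0.56. At a smaller effect every power in the table falls. The advantage of the two-visit adjusted contrast remains, because its signal is the sum of the other two terms at any effect size. It does assume that the effect is similar at both post visits.

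**What to change.** Replace the Part 2 sentence with one analysis for the primary and each secondary outcome:

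- A linear mixed model on the two post-training scores, with group, visit, group-by-visit, the baseline score as a fixed covariate and a random participant effect. Participants are analysed in the group to which they were allocated.
- One primary contrast named in advance, for example the adjusted between-group difference averaged over both post visits, with its 95% confidence interval.
- For the primary outcome, a single informational masking summary per person, defined in advance from the 30 conditions.
- No optional covariates.

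Delete the separate two-way ANOVA. Reword the SSQ sentence to say that scores are compared between groups, in line with the Abstract, and label changes within each arm as descriptive.

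This model keeps a participant who misses only one post-training visit. It does not recover anyone with no post-training score, so those losses should be reported by group.

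The cost is analysis wording only, with no new data or visits; the SPSS version already named can fit the model. The Study status section says allocation has not yet taken place, so the change can be made before any comparison by group exists.
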